## Abstract

**Background:**

Patients with BRAF V600E mutated metastatic colorectal cancer (mCRC) have a poor prognosis. The introduction of BRAF targeted therapy with encorafenib and weekly administered cetuximab have shown improved survival with a median progression free survival (PFS) of 4.3 months. However, a regimen with cetuximab given every second week may have comparable efficacy and is more convenient for patients. While BRAF targeted therapy is a new standard therapy in pre-treated patients with BRAF V600E mutated mCRC, resistance invariably occurs and is an emerging challenge. The aim of this study is to investigate the efficacy and tolerability of cetuximab given every second week in combination with daily encorafenib and to explore the correlation between markers of resistance and outcome.

**Methods:**

The study is an open label, single arm, phase II study, investigating the efficacy and tolerability of cetuximab given every second week in combination with encorafenib in patients with BRAF V600E mutated mCRC. Furthermore, we will be investigating mechanisms of response and resistance against BRAF targeted therapy though comprehensive genomic profiling on tumor tissue and blood for circulating tumor DNA analysis. A total of 53 patients (19 + 34 in two steps) will be included according to Simon’s optimal two stage design. The primary end point of the study is 2 months PFS rate.

**Discussion:**

By combining BRAF inhibitor with cetuximab given every second week we can halve the number of visits in the hospital compared to the currently approved regimen with weekly cetuximab. This seems particularly relevant in a group of patients with a median overall survival of 9.3 months. Resistance after initial response to targeted therapy can be either adaptive (e.g., epigenetic, or transcriptomic alterations) or acquired (selective genetic alterations - e.g., activating de novo mutations) resistance. It is of great importance to untangle these complex mechanisms of resistance in patients with BRAF V600E mutated mCRC to improve treatment strategies in the future potentially even further.

**Trial registration:**

EU Clinical Trial Register, Eudract no. 2020-003283-10. Registered on 11 November 2020.

## Background

Colorectal cancer (CRC) is among the most prevalent cancer diseases worldwide accounting annually for more than 1.900.000 new cases, and around 940.000 deaths [1]. Despite optimized surgical procedures and adjuvant combination chemotherapy, many patients still experience disease recurrence, most often with a fatal course. CRC is a heterogeneous disease based on its genetics, but for many years treatment of metastatic CRC (mCRC) has been limited to chemotherapy alone. However, in recent decades the treatment strategies have evolved because of the progress in our understanding of cancer as a disease of the genome and advances in molecular diagnostics. In mCRC, the significance of being able to detect *RAS* mutational status is one example that have led to improved results with the introduction of monoclonal antibodies (such as cetuximab and panitumumab) [2–4] – in 2013 the therapeutic indication was restricted by the European Medicines Agency (EMA) to patients with *RAS* wild-type mCRC tumors only [5]. Later it became possible to target tumors with deficient mismatch repair (dMMR) which often (in sporadic CRC cases) is caused by methylation of the *MLH1* gene promotor [6–8]. Based on the KEYNOTE-177 trial [9] programmed death 1 (PD-1) blockade with pembrolizumab is now standard of care to patients with dMMR mCRC.

Targeting BRAF in CRC has been under investigation [10–12] and this is highly clinically relevant since patients with mutated BRAF V600E mCRC have a very poor prognosis [13].

*BRAF* encodes the BRAF protein and a missense mutation of the gene – the single nucleotide substitution (T > A at codon 1799), resulting in the protein variant V600E – accounts for the vast majority of the *BRAF* mutations*.* The BRAF V600E mutation results in a constitutively activation of the mitogen-activated protein kinase (MAPK) pathway, which drives cellular proliferation and survival [14]. The incidence of BRAF V600E mutation in CRC is described to be around 10% in patients in clinical trials [15], but as high as 20% in unselected Nordic populations [16, 17].

Response to treatment with BRAF inhibitors (BRAFi) is extremely dependent on the origin of the *BRAF* mutated tumor. BRAF V600E mutated melanoma respond to BRAFi monotherapy with response rates (RR) of more than 50% [18] and in combination with MEK inhibitor (MEKi) survival is further prolonged [19–21]. In mCRC, BRAFi has very limited efficacy as monotherapy (RR around 5% [22]) and in combination with MEKi, whereas, targeting BRAF in combination with epidermal growth factor receptor (EGFR) has shown promising antitumor activity and survival benefits in the BEACON trial [12], where pre-treated patients with BRAF V600E mutated mCRC were randomized to receive treatment with either encorafenib with weekly cetuximab (doublet BRAF targeted therapy) or encorafenib with weekly cetuximab and binimetinib (triplet BRAF targeted therapy) or investigator’s choice of chemotherapy-based treatment.

Triplet therapy increased RR to approximately 26% and median progression free survival (PFS) to 4.3 months – and updated analysis found that doublet and triplet therapy resulted in similar overall efficacy across endpoints including PFS and overall survival (OS) [23]. These results led the United States Food and Drug Administration (FDA) to approve the doublet regimen: Cetuximab administered weekly in combination with encorafenib, on April 8th, 2020, to pre-treated patients with BRAF V600E mutated mCRC. The regimen with weekly cetuximab was approved by EMA in June 2020 and is considered a new standard therapy to patients with pre-treated BRAF V600E mutated mCRC.

A regimen with weekly intravenous therapy entails many visits in the hospital, however a regimen where cetuximab is given once every second week at a double dose, seems to have efficacy and tolerability comparable to weekly therapy, and is much more convenient for patients [24–31].

While BRAF targeted therapy in mCRC is a new standard of care, with a significant antitumor activity, rapid resistance against the therapy is an emerging challenge. It is of great importance to understand these mechanisms of resistance to ensure further development within the field of personalized therapy for patients with BRAF mutated CRC.

### Rationale of the study

The purpose of this study is to evaluate the efficacy and tolerability of biweekly cetuximab combined with standard dose encorafenib in patients with pre-treated BRAF V600E mutated mCRC. Furthermore, we wish to obtain a better understanding of mechanisms of response and resistance to BRAF targeted therapy in patients with mCRC.

## Design and methods

### Study design

The study is an open label, single arm, multicenter, phase II study.

### Eligible criterias

All patients must provide written informed content before inclusion in the study.

Eligible patients must be above the age of 18 years, WHO performance status of 0-1, and have histologically verified BRAF V600E mutated CRC, adenocarcinoma, proficient mismatch repair (pMMR), non-resectable and/or metastatic disease, and they must have received prior systemic treatment for CRC.

Measurable and/or evaluable non-measurable disease, and tumor lesion accessible for biopsy, is mandatory. Furthermore, included patients must have adequate haematological, cardiac and organ function. Finally, prior treatment with any EGFR-, RAF- or MEK-inhibitor is prohibited, and the patient is not allowed to have any known activating *RAS* mutation present at baseline.

### Treatment

The patients will be treated in cycles of 28 days.

Encorafenib will be administered once daily, orally, as a fixed dose, 300 mg once daily day 1-28.

Cetuximab will be administered as intravenous infusion on study site according to institutional standards (which includes premedication prior to each infusion), in dosage 500 mg/m^2^ every second week on day 1 and day 15 of each cycle.

Treatment will continue until progressive disease (PD), unacceptable adverse effects or patients wish of ending treatment.

Before starting study treatment, a baseline computed tomography (CT) scan will be performed, and new CT scans will be performed after every second cycle to evaluate response to treatment.

Response to treatment will be evaluated – when possible – according to the Response Evaluation Criteria in Solid Tumors (RECIST) version 1.1.

### End points

The primary endpoint of the study is 2 months PFS rate. Secondary endpoints include OS, PFS, RR according to RECIST version 1.1 – in patients with measurable disease – and toxicity.

Exploratory endpoints are correlation between tumor markers, markers of resistance and markers of tumor evolution and outcome.

### Statistics

The sample size is based on Simon’s optimal two stages design [32]. This design ensures early study termination if there is insufficient effect.

Patients with BRAF V600E mutated mCRC are at high risk of immediate progression with standard chemotherapy. In the BEACON study, the 2 months PFS rate was around 84%. A 2 months PFS rate less than 60% is not considered clinically acceptable. Assuming a significance level at 0.05 (α = 0.05) and a power at 90% (β = 0.10) it can be calculated that 19 patients should be included in the first part of the study. The enrollment will continue until 19 patients have received 2 months of therapy. If 12 or less out of the first 19 patients continue therapy beyond 2 months without PD, we will reject our hypothesis and close the study after the first stage of accrual.

If 13 or more patients continue therapy for at least 2 months without PD, an additional 34 patients will be accrued in the second stage. If at least 38 out of 53 patients continue therapy beyond 2 months without PD we will conclude that the treatment is effective enough to continue with future studies.

PFS and OS will be estimated using the Kaplan-Meier method. PFS will be calculated from time of trial inclusion till progression either by RECIST, clinically or death. OS will be calculated from time of trial inclusion to death.

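### The go/no-go rule counts patients still on therapy without PD, while the primary endpoint and planning rates are 2-month PFS, so the decision can contradict the endpoint

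*Protocol article*

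**What the plan says.** All references are to the protocol article.

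- **End points:** "The primary endpoint of the study is 2 months PFS rate".
- **Statistics, planning rates:** both are PFS rates. "A 2 months PFS rate less than 60% is not considered clinically acceptable", and "In the BEACON study, the 2 months PFS rate was around 84" per cent.
- **Statistics, PFS definition:** "PFS will be calculated from time of trial inclusion till progression either by RECIST, clinically or death". Stopping treatment is not an event.
- **Treatment:** "Treatment will continue until progressive disease (PD), unacceptable adverse effects or patients wish of ending treatment". Two of these three reasons are not progression.
- **Statistics, decision rule:** the study closes if 12 or fewer of the first 19 patients stay on therapy past 2 months without PD. The go sentence begins "If 13 or more patients continue therapy for at least 2 months without PD" and adds 34 patients. The final sentence is "If at least 38 out of 53 patients continue therapy beyond 2 months without PD we will conclude that the treatment is effective enough".
- **Statistics, stage 1 accrual:** enrolment is said to run until 19 patients have had 2 months of treatment, whereas the closing rule refers to the first 19 patients.

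**The concern.** The rule requires two things, still on therapy and no PD. The endpoint requires only that the patient is alive without progression. They differ for one kind of patient: off treatment before 2 months because of toxicity or personal choice, but alive and progression-free at 2 months. That patient adds to the 2-month PFS rate and is lost from the decision count.

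The rule as written is thus closer to a time-to-treatment-failure criterion, held against thresholds set for PFS. This is the trial's only formal decision rule. At stake is closing after 19 patients, or declaring the regimen insufficient after 53, when the PFS count itself would have passed. The reported primary endpoint and the formal conclusion could then disagree.

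Two smaller faults sit in the same paragraph. The stage 1 denominator is described in two ways. The closing sentence counts patients continuing *beyond* 2 months, while the go sentence counts those continuing *for at least* 2 months.

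**Working it through.** **Inputs from Statistics.** Stage 1: n1 = 19, close at 12 or fewer successes. Total N = 53, effective at 38 or more (r = 37). α = 0.05, power 90%. Unacceptable rate 60%; reference rate 84%.

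**Formula.** For success probability q per patient:

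- P(effective) = Σ over x = 13..19 of P(X1 = x) · P(X2 ≥ 38 − x), with X1 ~ Bin(19, q) and X2 ~ Bin(34, q)
- P(close at stage 1) = P(X1 ≤ 12)

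**Step 1: the plan's own design.** A full search for Simon's optimal design (smallest expected N at 60%, α = 0.05, power 90%) gives:

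| Alternative | Optimal design | Type I error | Power |
|---|---|---|---|
| 80% | 12/19, 37/53 | 4.3% | 90.1% |
| 84% | 9/14, 23/32 | 4.9% | 90.6% |

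The stated design reproduces exactly at 80%, a rate the article does not give. At 84%, the stated 12/19 and 37/53 rule has 97.3% power.

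**Step 2: the rule as written.** Let p be the true 2-month PFS rate and d the share of progression-free patients off therapy by 2 months. The document gives no value for d, so 2% to 10% is an assumed range. Counting early stoppers as failures, the success probability becomes q = p(1 − d). Example: p = 0.84 and d = 0.05 give q = 0.84 × 0.95 = 0.798.

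| p | d | q | Power | Closed at stage 1 |
|---|---|---|---|---|
| 84% | 0 | 0.840 | 97.3% | 2.3% |
| 84% | 2% | 0.823 | 95.1% | 3.8% |
| 84% | 5% | 0.798 | 89.6% | 7.1% |
| 84% | 10% | 0.756 | 72.5% | 15.9% |
| 80% | 0 | 0.800 | 90.1% | 6.8% |
| 80% | 2% | 0.784 | 85.0% | 9.5% |
| 80% | 5% | 0.760 | 74.6% | 14.9% |
| 80% | 10% | 0.720 | 51.9% | 26.6% |

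**Step 3: how much early stopping is tolerable.** Power is exactly 90% at q = 0.7996. At p = 84% this is reached at d = 1 − 0.7996/0.84 = 4.8%. At p = 80% there is almost no slack.

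**Step 4: direction.** At a true PFS of 60%, type I error falls from 4.3% to 1.6% (d = 5%) and 0.5% (d = 10%).

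**Step 5: how often the two counts disagree.** Every on-therapy success is also a PFS success, so whenever the rule passes, the PFS count passes too. The chance that PFS passes and the rule fails is therefore the difference in power:

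- p = 84%: 97.3 − 89.6 = 7.7 points (d = 5%); 97.3 − 72.5 = 24.8 points (d = 10%).
- p = 80%: 90.1 − 74.6 = 15.5 points (d = 5%); 90.1 − 51.9 = 38.2 points (d = 10%).

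The reverse disagreement cannot occur.

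**The case against.** **The wording may be loose shorthand for PFS.** This is possible, but all three decision sentences tie success to staying on therapy and the accrual sentence also speaks of treatment received. No sentence says that a progression-free patient off therapy counts as a success. An article may condense a protocol, but here a stated rule conflicts with a stated endpoint.

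**A reader might infer that the stated 90% power is simply lost.** The document does not support that. At 84%, the only favourable rate it gives, power stays at or above 90% until about 4.8% of progression-free patients are off therapy. The larger losses belong to 80%, which is inferred from the design. The stopping share is assumed throughout.

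**A reader might also infer a raised risk of a false positive.** Under the literal reading the opposite holds: the test becomes more conservative.

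**Early stoppers may not count as failures at stage 1.** The accrual sentence can be read as leaving them out of the 19. The stage 1 closure figures would then not apply, and the problem would be one of a selected denominator. This objection stands as a limit on the figures and is a reason to settle the denominator.

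**An on-therapy criterion is defensible.** The study aims at efficacy and tolerability, so such a go/no-go criterion could be chosen deliberately. It would then need to be named as such, with its own unacceptable and target rates. The article names PFS and gives PFS rates.

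**Beyond versus at least is largely editorial.** Agreed. Since 12 or fewer and 13 or more are complementary counts, a single quantity is evidently meant. The sentences conflict only if a patient stopping at exactly 2 months is decisive.

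**Conclusion.** The decision rule is wrong as written: it does not measure the primary endpoint whose thresholds it uses. Followed literally, it can close or fail the trial when the 2-month PFS count meets the bar.

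The loss is conditional. With 2% to 10% of progression-free patients off therapy by 2 months, power runs from 95.1% down to 72.5% at a true PFS of 84%, and from 85.0% down to 51.9% at 80%. These figures assume that early stoppers count as failures at both stages and that the stopping share is the same for all patients. They do not show that the trial is underpowered, because the actual share is unknown. The mismatch itself, the unsettled stage 1 denominator and the unstated alternative rate do not depend on these assumptions.

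**What to change.** - In all three rule sentences, define success as alive and without progression (RECIST or clinical) at the 2-month assessment, regardless of treatment status. Use one time wording throughout.
- Stage 1: count among the first 19 patients included; stop at 12 or fewer, continue at 13 or more. Final: count among all 53 included; effective at 38 or more. The cut-offs do not change.
- Replace the sentence that ties stage 1 accrual to 19 patients having received 2 months of therapy, so that it matches this denominator.
- State the alternative rate used for the design. The figures reproduce at 80%, not at 84%.
- Report treatment continuation at 2 months separately, as a tolerability outcome.

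If an on-therapy criterion is intended, the alternative is to name it as the endpoint and derive both planning rates for it.

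**Cost.** This is mostly wording, with no change in sample size. Patients who stop early need a disease assessment at 2 months. The PFS endpoint already implies one, but the Treatment section ties CT scans to treatment cycles, so some scans may be additional. At publication 13 patients had been included, fewer than the 19 needed for stage 1.

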### Biopsies and circulating tumor DNA (ctDNA) analysis

Fresh tumor biopsies, primarily from metastatic lesions, are obtained from patients at baseline, after two cycles of treatment (on-treatment), and upon progression of disease. Biopsies are either core needle biopsies (18-gauge needle) or surgical resections samples. Three samples are taken from the same lesion each time – one sample is formalin-fixed and paraffin-embedded (FFPE) for histopathological verification of the tissue and two samples, stored in RNAlater, are for comprehensive genomic analyses. A blood sample is collected at baseline and used for subtraction of germline variants to identify tumor specific mutations only.

Blood samples (collected in STRECK-tubes) for analysis of ctDNA are taken prior to each treatment cycle.

### Genomic profiling

DNA and RNA from each biopsy is extracted and purified to perform whole genome sequencing (WGS), RNA sequencing (RNAseq), and single nucleotide polymorphism (SNP) arrays. WGS is performed from tumor and germline DNA using Illumina polymerase chain reaction (PCR) free DNA prep, and RNAseq is performed from tumor RNA using Illumina Stranded Total RNA Prep. SNP array is performed with CytoScan HD/OncoScan array. The DNA and RNA libraries are sequenced on NovaSeq6000 (Illumina) as 2 × 150 bp paired-end sequencing. The raw data is mapped to the hg38/GRCh38 human reference genome using BWA-MEM v0.7.12 software and bioinformatics is done following Genome Analysis Toolkit (GATK) best practice.

Somatic mutations are identified by subtracting the germline variants from the tumor variants. RNAseq is performed to identify gene fusions and to evaluate expression levels of selected, predefined targets. SNP array analysis is performed to identify copy number alterations.

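### The only mapping rule, BWA-MEM to the genome, is worded to cover RNA as well as DNA reads, although it has no splice model; it should be limited to WGS (minor, exploratory analyses only)

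*Protocol article*

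**What the plan says.** Under Design and methods, Genomic profiling, the protocol article describes WGS, RNAseq and SNP arrays on each biopsy. The RNA assay is set out as follows: "RNAseq is performed from tumor RNA using Illumina Stranded Total RNA Prep". Both library types then share one sequencing sentence: "The DNA and RNA libraries are sequenced on NovaSeq6000 (Illumina) as 2 × 150 bp paired-end sequencing". The next sentence gives the mapping rule: "The raw data is mapped to the hg38/GRCh38 human reference genome using BWA-MEM v0.7.12 software". It ends with the statement that "bioinformatics is done following Genome Analysis Toolkit (GATK) best practice".

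The section goes on to somatic variants, found by subtracting germline from tumor variants, and then gives the purpose of the RNA data: "RNAseq is performed to identify gene fusions and to evaluate expression levels of selected, predefined targets". It names no second aligner and does not separate RNA reads from DNA reads at the mapping step.

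The End points section places the use of these data at the lowest level: "Exploratory endpoints are correlation between tumor markers, markers of resistance and markers of tumor evolution and outcome".

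**The concern.** BWA-MEM aligns reads to a contiguous genome sequence and has no model of introns. That suits WGS. A read from mature RNA that spans an exon junction does not match the genome contiguously, so this aligner will clip it, split it or, at times, misplace it.

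Both stated uses of RNAseq are sensitive to this. A gene fusion shows up as a split alignment, and an ordinary splice junction can look the same to an aligner without introns. Expression estimates depend on how many reads are assigned to each gene. Any loss at junctions varies with exon structure, so it would not be a constant factor that cancels when genes are compared.

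At stake is the RNA part of the resistance work. The Discussion describes adaptive resistance as partly transcriptomic and gives CRAF overexpression as an example from the literature. Among the assays in Genomic profiling, only RNAseq measures expression, so the other assays cannot make good an error there.

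**Working it through.** The plan gives no figure on this point, so there is nothing to reproduce. The check has three parts.

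**1. What the mapping sentence refers to.** The sequencing sentence has the DNA and RNA libraries as its subject. The mapping sentence follows directly and speaks of the raw data without qualification. Its nearest antecedent is the output of both library types. Read literally, BWA-MEM to hg38/GRCh38 is therefore the mapping step for both. The text does not say in so many words that RNA reads are mapped this way. The GATK clause and the somatic-variant sentence that follow would fit a DNA-only description.

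**2. What depends on it.**

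| Element of the plan | Section | Uses RNA mapping? |
|---|---|---|
| Primary endpoint, 2-month PFS rate | End points | No |
| OS, PFS, RR, toxicity | End points | No |
| Simon two-stage design, 19 + 34 = 53 | Statistics | No |
| Somatic mutations (WGS) | Genomic profiling | No |
| Copy number (SNP array) | Genomic profiling | No |
| ctDNA | Biopsies and ctDNA analysis | No |
| Gene fusions and expression from RNAseq | Genomic profiling | Yes |

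Only the last row is exposed.

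**3. Whether the size can be estimated.** The read length is 150 bases (Genomic profiling). Exon length L is not given, so it is an assumption here. For a read from mature RNA that starts uniformly within an internal exon of length L, the last 149 start positions carry it past the exon end. The share that crosses the next junction is therefore min(1, 149/L):

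- L = 300: 149/300 = 0.50
- L = 200: 149/200 = 0.75
- L = 120: 149/120 exceeds 1, so 1.0

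This is the share of reads that touch a junction, even by one base. It is not the share lost or miscalled. A 150-base read that crosses a single junction keeps a segment of at least 150/2 = 75 bases in one exon, and that segment can often still align and count toward its gene. The share is also lower in total-RNA libraries, the type used here, because they contain intronic reads. The arithmetic shows that junction reads are common enough to deserve correct handling. It does not give an expression error or a false-fusion rate. Those depend on the target genes, the downstream tools and their filters, none of which the article states.

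**The case against.** The strongest reply is that the sentence condenses the WGS pipeline. It runs on to GATK best practice and then to somatic variants, while RNAseq is described afterwards by purpose only. The article's wording is loose elsewhere: the Abbreviations list expands WGS as exome sequencing, whereas Genomic profiling says whole genome. On this view one unsplit noun phrase is weak evidence that anyone chose BWA-MEM for RNA. This stands as a limit: a reader might infer that RNA reads certainly are mapped with BWA-MEM, and the document does not establish that. It does not remove the point, because the rule as printed covers both data types, and a DNA-only intention would call for the same correction.

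A second reply is that a journal article may leave the gene annotation, fusion caller and quantification level to the full protocol. That is right, and their absence is not criticised here. The point rests on a stated rule, not an omitted one.

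A third reply concerns the consequence. A reader might infer that fusions and expression cannot be derived reliably at all, or that half or more of the RNA reads would be lost. Neither is shown. BWA-MEM does report split alignments, clipped reads can still be counted, and later filtering may remove false candidates. A reader might also infer that the whole exploratory endpoint would be distorted. That too goes beyond the text. End points does not list fusions or expression by name, CRAF overexpression is a literature example rather than a declared trial marker, and mutations, copy number and ctDNA do not depend on RNA mapping.

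**Conclusion.** The point holds as a minor one. As printed, the article gives one aligner without a splice model for DNA and RNA reads alike. Followed literally, that could bias RNA expression levels in a gene-dependent way and add false fusion candidates. The size cannot be estimated from the document.

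This rests on two things: the literal reading of the mapping sentence, which is natural but not certain, and the general property that BWA-MEM does not model introns, which the article does not discuss. The trial's decision rule and its conclusions on efficacy and tolerability are unaffected under either reading.

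**What to change.** Limit the BWA-MEM sentence to the WGS reads. Add one sentence stating that RNA reads are aligned to hg38 with a splice-aware aligner (STAR is one example) before fusion calling and expression quantification. If that is already the practice, only the text needs correcting.

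If any RNA data were mapped with BWA-MEM, re-map them where the raw reads are available; the article does not say whether they are kept. Status of the study reports 13 patients included at the time of writing, so the amount to reprocess at that stage would be small.

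The cost is a wording change and some computing time. No extra patients, samples or sequencing are needed, and the sample size does not change.
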